**Early-onset fetal growth restriction: gestational age <32 weeks**
Abdominal circumference or estimated fetal weight <3rd percentile or umbilical artery absent end-diastolic flowORAbdominal circumference or estimated fetal weight <10th percentile *combined with*Uterine artery pulsatility index >95th percentile *and/or*Umbilical artery pulsatility index >95th percentile
**Late-onset fetal growth restriction: gestational age ≥32 weeks**
Abdominal circumference or estimated fetal weight <3rd percentileORAt least 2 of the following 3:Abdominal circumference or estimated fetal weight <10th percentileAbdominal circumference or estimated fetal weight crossing >2 quartiles (50 percentiles) on growth charts (growth centiles are noncustomized)Cerebroplacental ratio <5th percentile or umbilical artery pulsatility index >95th percentile

### Data and Sample Collection

This study involves the collection of comprehensive maternal data, including demographics, medical and obstetric history, clinical assessments throughout pregnancy and delivery, and maternal biological samples.

#### Demographic and Clinical Data

Maternal demographic characteristics, medical and obstetric history are collected by research midwives, sonographers, and clinical research fellows at enrollment through face-to-face conversations or electronic medical records. Maternal risk factors are recorded in accordance with the National Institute for Health and Care Excellence (NICE) [33] and American College of Obstetricians and Gynecologists (ACOG) guidelines [34]. Clinical data, including routine ultrasound screenings, laboratory tests, and maternal and perinatal outcomes, are obtained from integrated electronic medical records.

#### Ultrasound and Biophysical Measurements

Ultrasound assessments, including fetal biometry, maternal and fetal Doppler ultrasound, and maternal ophthalmic artery Doppler, are performed by certified sonographers or MFM specialists in accordance with the International Society of Ultrasound in Obstetrics and Gynecology recommendations and guidelines [35-37]. Maternal cardiovascular function is evaluated through additional measurements, including blood pressure (BP) and arterial stiffness assessments. BP is measured using an Omron automated device (OMRON Healthcare Inc) following a standardized protocol, with MAP calculated as (2/3 diastolic BP + 1/3 systolic BP) based on the average of 2 stable readings [38]. Arterial stiffness, measured as augmentation index, is assessed using the Uscom BP+ device (USCOM Limited), according to the manufacturer’s guidelines.

#### Biological Sample Collection

All biological specimens are collected, processed, and stored according to standard operating procedures by trained research staff. At each visit, 15 mL of maternal blood and 5 mL of urine are collected. For serum collection, blood is collected in a nonanticoagulant vacutainer and allowed to coagulate at room temperature for 30 to 60 minutes, followed by centrifugation at 1300×*g* for 15 minutes at room temperature. Plasma samples are collected in an EDTA-treated vacutainer and immediately centrifuged at 1900×*g* for 15 minutes at room temperature. For RNA analysis, whole-blood samples are collected into PAXgene Blood RNA tubes, gently inverted 10 times for homogenization, stored upright at room temperature for 2 hours or longer, frozen at −20℃ for 24 hours, and stored at –80 ℃ for long-term preservation [39]. Random midstream urine samples are collected in sterile urine collection vials. Aliquots of serum (0.5 mL), plasma (0.5 mL), and urine samples (1 mL) are stored in 1.8 mL microtubes at –80 ℃.

#### Maternal Circulating Biomarker Measurements

Collected biological samples will be analyzed for maternal circulating biomarkers. Maternal serum levels of PlGF and sFlt-1 will be quantified using the KRYPTOR Compact Plus immunoanalyzer (BRAHMS Thermo Fisher Scientific), followed by calculation of the sFlt-1:PlGF ratio and multiples of the expected median using previously published equations [40,41]. In addition, exploratory omics analyses of maternal circulating biomarkers will be conducted using a nested case-control design on a subset of participants, using techniques such as quantitative polymerase chain reaction and liquid chromatography with quadrupole time-of-flight mass spectrometry.

### Statistical Analysis Plan

All statistical analyses will be conducted using the R statistical environment (R Foundation for Statistical Computing).

#### Sample Size Estimation

We estimate a 10% to 15% participation rate from the approximately 5000 annual deliveries at GCUH. On the basis of a prevalence of 10% for placental dysfunction–related disorders (preeclampsia and SGA or FGR), approximately 200 cases with these outcomes are expected. In the development of prediction models using binary outcomes (high-risk or low-risk) with a 10% incidence rate and up to 15 predictors, targeting an area under the receiver operating characteristic curve (AUC-ROC) of 0.75, the estimated sample size is approximately 1700 participants [42].

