### Study Objectives

#### Primary Objectives

The primary objectives of this study are as follows:

To improve current predictive models or develop new predictive models for placental dysfunction–related pregnancy complications, including preterm preeclampsia and FGR, at 2 critical gestational periods: the first trimester (11‐13 weeks) and the second trimester (26‐28 weeks)To establish third-trimester (35‐36 weeks) models to predict term preeclampsia and FGR and to define the optimal time for delivery.

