These advancements in preterm preeclampsia screening have prompted updates to national [50,51] and international [52] guidelines, recommending implementation of the prediction model with prophylactic low-dose aspirin to reduce preterm preeclampsia incidence and associated adverse outcomes. A cost-effectiveness analysis in Australia demonstrated significant benefits of this screening strategy, including prevention of 31 preterm preeclampsia cases and cost savings of approximately Aus $1.43 million (Aus $1=US $0.72 as of August 27, 2020) over a 2-year period [53]. Despite these clinical benefits, the FMF first-trimester prediction model has not yet become a standard component of routine maternity care for all health care providers in Australia. Gold Coast University Hospital has implemented FMF-based first-trimester preeclampsia screening in routine clinical care, providing a valuable setting to generate evidence supporting broader application in clinical practice.

Current prediction models still have limited accuracy for predicting term preeclampsia and SGA due to their complex etiology. Although considered less severe, term complications constitute most cases, occurring at least twice as frequently as preterm preeclampsia, and impose a significant health care burden [26]. While the first-trimester screening combined with low-dose aspirin effectively prevents preterm preeclampsia, it showed limited efficacy for term preeclampsia [24]. A prediction model at 35 to 36  weeks’ gestation, using maternal factors and biomarkers, can identify approximately 70% of pregnancies at risk of developing term preeclampsia [54]. In addition, planned birth at term is a potential prevention strategy for term preeclampsia [55,56]. A recent secondary analysis from a prospective nonintervention cohort study has demonstrated that a risk-stratified approach based on a combined prediction model at 35 to 36  weeks’ gestation with timed birth is likely able to reduce the risk of term preeclampsia [27]. However, research on individualized risk assessment models at late gestation to determine optimal delivery timing remains limited. This cohort study will facilitate the development of refined prediction models and optimal delivery timing strategies to reduce term preeclampsia incidence and improve pregnancy outcomes.

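### The sample size is justified for a 10% composite outcome, but the primary objectives name rarer component outcomes to which the 1700 participants and 15 predictors do not carry over

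*Protocol article*

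**What the plan says.** The Sample Size Estimation section of the protocol article takes a 10% prevalence for placental dysfunction-related disorders, explained in brackets as preeclampsia and SGA or FGR. From this it states that "approximately 200 cases with these outcomes are expected". It then sizes model development "using binary outcomes (high-risk or low-risk) with a 10% incidence rate and up to 15 predictors". The planning AUC is 0.75, and the section concludes that "the estimated sample size is approximately 1700 participants". No event count or sample size is given for any narrower outcome.

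The Primary Objectives are narrower. Objective 1 concerns placental complications "including preterm preeclampsia and FGR, at 2 critical gestational periods" (11-13 and 26-28 weeks). Objective 2 concerns third-trimester "models to predict term preeclampsia and FGR and to define the optimal time for delivery". The section defining preeclampsia and FGR splits preeclampsia at delivery before or from 37 weeks, so the preterm and term forms exclude each other. The Discussion describes term complications as "occurring at least twice as frequently as preterm preeclampsia".

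The section on prediction model development enters predefined candidates, reduces the model (backward elimination at P<.10 is the example) and tests polynomial terms up to cubic. The Results report 1267 enrolled at close of recruitment, of whom 51 were withdrawn or had missing or duplicated data.

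**The concern.** The number of candidate parameters a logistic model can carry depends on the number of events and on how well the predictors discriminate. A calculation for a 10% outcome does not apply to a component of that outcome, unless the component makes up nearly all of it. Here the only stated justification is for the composite, while the objectives name its parts. For the rarest part, preterm preeclampsia, up to 15 candidates could enter the model with a justification that belongs to another outcome. The likely result is overfitting: coefficients too extreme, a calibration slope below 1, and a risk threshold that does not reproduce its screen-positive rate in new women. Recruitment has closed, so more events cannot be collected; only the models can still be adjusted.

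**Working it through.** **Inputs from the article.** Composite incidence 10%, up to 15 predictors, AUC 0.75, about 1700 participants and about 200 cases (Sample Size Estimation). Term disease at least twice as frequent as preterm preeclampsia (Discussion). Available participants 1267 − 51 = 1216 (Results). Existing FMF model: 75% detection of preterm preeclampsia at a 10% screen-positive rate (Introduction).

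**Assumptions.** A shrinkage target S = 0.90, which the article does not state, and a normally distributed linear predictor with equal variance in events and non-events, used to turn an AUC and an incidence into a Cox-Snell R².

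**Formula.** n = P / [(S − 1) · ln(1 − R²/S)], with P the number of candidate parameters. Turned round, P = n · (S − 1) · ln(1 − R²/S).

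**Step 1: reproduce the stated size.** At 10% and AUC 0.75, R² = 0.0752. Then n = 15 / [−0.1 × ln(1 − 0.0752/0.9)] = 15 / 0.008725 ≈ 1,720, about 172 events. This agrees with the stated 1700. The other two usual criteria (optimism in Nagelkerke R², precision of the overall risk) give 596 and 139 and do not bind.

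**Step 2: ceiling for preterm preeclampsia.** If the whole 10% were preeclampsia and the ratio exactly 2:1, preterm preeclampsia would be 10% / 3 = 3.33%.

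- Planned 1700: 1700 × 0.0333 ≈ 57 events, 57/15 = 3.8 per predictor.
- Stated 200 cases: 200 / 3 ≈ 67 events, 4.4 per predictor.
- Available 1216: 1216 × 0.0333 ≈ 40 events, 2.7 per predictor.

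Any share of the 10% that is SGA or FGR without preeclampsia lowers these. Women could join at any stage before 37 weeks, so no single window holds more than the full cohort.

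**Step 3: the same criterion at 3.33%.** The last AUC comes from the FMF detection rate, treating the 10% screen-positive rate as the false-positive rate: separation 0.674 + 1.282 = 1.956, and AUC = Φ(1.956/√2) ≈ 0.917.

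| AUC | R² | n for 15 parameters | Parameters supported by 1216 |
|---|---|---|---|
| 0.75 | 0.028 | about 4,690 | 3.9 |
| 0.85 | 0.063 | about 2,060 | 8.9 |
| 0.90 | 0.091 | about 1,400 | 13.0 |
| 0.917 | 0.103 | about 1,230 | 14.8 |

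At the planned 1700, the supported number is 5.4 at AUC 0.75 and 12.4 at AUC 0.85.

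**Step 4: range for the unknown split.** If preeclampsia were half of the composite (assumption), the ceiling is 1.67%, about 20 events in 1216. That supports about 2 parameters at AUC 0.75 and about 7 at 0.90. For a component at an assumed 5%, such as FGR, 1216 supports about 5.7 at AUC 0.75. For term preeclampsia at an illustrative 6.67%, 15 parameters need about 2,460 participants at AUC 0.75.

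**Step 5: what counts as a parameter.** Candidates later eliminated and polynomial terms tested both count. One continuous predictor examined up to a cubic uses three parameters, so 15 predictors can mean more than 15 parameters.

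**The case against.** The strongest reply is that AUC 0.75 is the wrong planning value for preterm preeclampsia. The FMF performance quoted in the article implies about 0.917, at which 15 parameters need about 1,230 participants, almost exactly what is available. This stands as far as it goes, and it removes most of the shortfall if three things hold together: the new model discriminates that well, the whole 10% is preeclampsia, and no more than 15 parameters are examined. The article states none of these, and its own planning value is 0.75.

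Second, separate models are an inference. The article nowhere says that each component gets its own model, and the description of the competing-risks analysis brackets the outcome as preeclampsia or FGR. That is fair. Still, the objectives, the preterm/term split and the separate FGR and preterm preeclampsia risks in Table 1 point to separate targets. If a composite is meant, the objectives need to say so.

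Third, the limit of 15 is an upper bound, outcome-specific candidate lists often sit in an analysis plan that is not shown, and updating of FMF risk and cross-validated calibration are already planned. All true. But the stated updating uses markers from the two later windows, logistic regression remains the primary approach, and cross-validation shows overfitting without preventing it. What the article does state, its sample-size justification, applies to a different outcome.

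**Conclusion.** The point holds in a limited form. The stated size and predictor allowance apply to the 10% composite and do not carry over to preterm preeclampsia at the article's own AUC of 0.75: about 4,690 participants would be needed, and 1216 support about 4 parameters. At higher AUCs the gap narrows, to just under 15 parameters at 0.917, and it widens again as SGA or FGR takes a larger share of the composite. The shortfalls for term preeclampsia and FGR cannot be fixed, because the article does not split the 10%.

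This rests on the assumed shrinkage target of 0.90 and the normal linear predictor, both supported by the close reproduction of 1700, and on the article's general 2:1 ratio applying to this cohort.

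Three stronger readings are tempting and not supported:

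- A reader might infer that preterm preeclampsia models would be unreliable even with 1700 participants. At the 3.3% ceiling with AUC 0.90, about 1,400 would suffice.
- A reader might take 40 events as what the plan itself implies. That figure uses achieved enrolment; the planning figures give 57 or 67.
- A reader might conclude that a 15-predictor model is committed to preterm preeclampsia, or that only a handful of new markers can ever be added. The article sets only an upper bound, and the supportable number depends on the AUC.

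**What to change.** 1. State in Sample Size Estimation that the calculation covers the composite only, and give expected events for each outcome and window.
2. Before fitting, cap the candidate parameters for each outcome and window from the observed events, using the same criterion and a stated outcome-specific AUC. Count polynomial terms and candidates that may later be eliminated.
3. Where the cap cannot hold the planned candidates, make one of these the primary approach: updating the existing FMF risk (already planned for the later windows), penalised estimation, or a model for the composite, declared as such in the objectives.

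The cost is wording and some model discipline, with no new recruitment. The downside is that fewer novel markers can be tested for the rarest outcome.

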## Results

Recruitment for the Placental Health Study commenced in June 2022. By the close of recruitment in February 2026, a total of 1267 participants were enrolled. Of these, 1072 (84.6%) participants had a completed pregnancy, 144 (11.4%) participants are still to complete their pregnancy, and 51 (4%) had withdrawn or with missing or duplicated data. Comprehensive clinical data, including maternal demographics, medical and obstetric history, ultrasound measurements, Doppler indices, hemodynamic parameters, pathology laboratory results, and pregnancy outcomes, were collected through integration with electronic medical records (Table 1). Data were recorded in REDCap. Maternal serum, plasma, whole blood for RNA extraction, and urine samples have been collected and processed according to standardized operating procedures. Biospecimens are stored at −80 °C.

**Table 1. T1:** Summary of data and sample collection throughout pregnancy.

Assessment period and category	Data collected
At enrollment	
Demographic data	Date of birth, age, height, weight, BMI, ethnicity, smoking, and alcohol use status
Medical history	Diabetes mellitus, chronic hypertension, systemic lupus erythematosus, and antiphospholipid syndrome
Obstetric history	Miscarriage, termination, parity, previous preterm birth, preeclampsia, FGR^a^, placental abruption, and placenta previa
Risk assessment	Preeclampsia risk scoring (NICE^b^ and ACOG^c^ guidelines)
11‐13 weeks assessment	
First-trimester risk assessment	NIPT^d^ results (risk of trisomies, fetal sex, risk of monosomy X, sex chromosome aneuploidy risk, 22q11.2 deletion risk, and fetal fraction [cfDNA^e^, %], FGR risk, and preterm preeclampsia risk
Ultrasound and Doppler	Fetal biometry (CRL^f^ and NT^g^), fetal Doppler (ductus venosus A-wave), maternal Doppler (right and left uterine artery PI^h^ and mean PI), biophysical markers (cervical length and measurement method), and ultrasound markers (nasal bone, tricuspid regurgitation, cardiac activity, FHR^i^, holoprosencephaly, diaphragmatic hernia, atrioventricular septal defect, exomphalos, and megacystis)
BP^j^	Systolic BP, diastolic BP, and MAP^k^
Biochemical markers	Free beta-hCG^l^, PAPP-A^m^, PlGF^n^, sFlt-1^o^, and sFlt-1:PlGF ratio
Clinical pathology	Urine test, full blood count, chemistry panel, and recent iron infusion date (if available)
26‐28 and 35‐36 weeks	

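### Recruitment closed at 1267 against a stated requirement of about 1700, and the ceiling of 15 predictors was neither lowered nor qualified

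*Protocol article*

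**What the plan says.** All references are to the protocol article.

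- **Sample Size Estimation** first gives a recruitment outlook: "We estimate a 10% to 15% participation rate from the approximately 5000 annual deliveries at GCUH". From a 10% prevalence of preeclampsia and SGA or FGR together, it says that "approximately 200 cases with these outcomes are expected".
- The same section then sizes the models separately, "with a 10% incidence rate and up to 15 predictors" and "targeting an area under the receiver operating characteristic curve (AUC-ROC) of 0.75", and concludes that "the estimated sample size is approximately 1700 participants".
- **Results**: "By the close of recruitment in February 2026, a total of 1267 participants were enrolled". Of these, 1072 have a completed pregnancy, 144 are still pregnant, and "51 (4%) had withdrawn or with missing or duplicated data". The abstract gives the same counts.
- **Discussion**, limitations: singletons only, single centre, unmeasured predictors, and cost or difficulty of some markers. Sample size is not mentioned.

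**The concern.** The 1700 is the only size justification for the primary objective, and it is what supports the ceiling of 15 predictors. Recruitment is over, so the gap to 1267 is final. The article prints both numbers without comparing them and leaves the ceiling unchanged. A reader would take a 15-predictor model from this cohort as adequately sized by the article's own standard, and it would not be. Too many parameters for the events available give predictions that are too extreme and a calibration slope below 1 in new women.

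The section also carries two totals. About 200 cases at 10% implies about 2000 participants, and the model calculation asks for about 1700. They are not reconciled, and neither was reached.

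**Working it through.** **Inputs from the article.** Incidence 10%, 15 predictors (taken as 15 parameters), AUC 0.75, stated n about 1700, stated cases about 200 (Sample Size Estimation); 1267 enrolled, 1072 completed, 144 ongoing, 51 withdrawn, missing or duplicated (Results). 1267 − 51 = 1216 = 1072 + 144.

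**Assumptions, not in the article.** Expected shrinkage S = 0.90, and a linear predictor that is normal with equal variance in cases and non-cases. The section cites a source for its method that is not available here.

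**1. Reproducing the 1700.** For AUC 0.75 at prevalence 0.10, the Cox-Snell R² is 0.0752 (maximum 0.478). The shrinkage criterion is

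n = P / [(S − 1) ln(1 − R²/S)].

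With P = 15 and S = 0.90: R²/S = 0.0836, ln(1 − 0.0836) = −0.0873, and n = 15 / 0.008725 ≈ 1719. The other usual criteria need fewer: 596 for optimism in R² of at most 0.05, and 139 for overall risk within ±0.05. Two alternatives fit less well: R² set at 15% of its maximum gives 1807, and 10 events per predictor gives 1500. The 1700 is therefore sound under the assumed criterion.

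**2. Shortfall.** 1267/1700 = 74.5% (433 short). 1216/1700 = 71.5% (484 short).

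**3. What the achieved numbers support**, for the 10% composite. Parameters at S = 0.90 are n × 0.008725. Shrinkage at 15 parameters solves the formula above for S.

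| n | Cases at 10% | Events per predictor, 15 predictors | Parameters at S = 0.90 | Shrinkage with 15 |
|---|---|---|---|---|
| 1700 | 170 | 11.3 | 14.8 | 0.90 |
| 1267 | 127 | 8.4 | 11.1 | 0.87 |
| 1216 | 122 | 8.1 | 10.6 | 0.86 |
| 1072 | 107 | 7.1 | 9.4 | 0.85 |

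Under the simpler rule of 10 events per predictor, 122 cases allow 12. Both rules fall below 15.

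**4. The second total.** 200 / 0.10 = 2000 participants. At the lower participation rate, 10% of 5000 is 500 a year, so four years would give 2000; the section states no duration.

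**5. Why step 3 is a best case.**
- The 10% is a composite. The Primary Objectives section names preterm preeclampsia, term preeclampsia and FGR, each necessarily rarer. The article gives no incidence for them. Over an assumed 2% to 5%, 1216 women yield 24 to 61 cases. Fifteen parameters at the same AUC and S would need about 7650 to 3200 women, so 1216 support about 2 to 6 (15 × 1216/7652 = 2.4; 15 × 1216/3200 = 5.7).
- Models are built in three gestational datasets, and Recruitment and Retention allows entry at any stage before 37 weeks. A woman who joins late cannot contribute to an earlier window. No counts by window are given.
- Primary Objectives: Prediction Model Development tests polynomial terms up to cubic, so 15 predictors can use more than 15 parameters.

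**The case against.** Several defences deserve weight.

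- *The 200 cases are not an arithmetic slip.* A reader might infer that 200 was meant as 10% of 1700, which is 170. The article does not say so. The 200 follows the participation estimate and precedes the 1700, so it reads as a recruitment projection of unstated duration. Only the lack of reconciliation stands.
- *The 1700 is not wrong.* It reproduces closely. What failed is accrual and the updating of the plan.
- *The 0.90 is not the article's stated rule.* That is correct, so a cap of exactly 10 cannot be presented as the article's own. The range of 10 to 12 covers both rules, and the loss of 15-predictor capacity holds under either.
- *Fifteen is a ceiling, and overfitting will be checked.* Repeated 5-fold cross-validation with calibration slope and intercept would reveal overfitting. It would not correct the coefficients, and the article names no shrinkage or penalised method. Still, a fall from 0.90 to about 0.86 does not support a claim that the composite models will be badly overfitted.
- *The numbers are disclosed.* The enrolment and the 51 records appear openly, and the article does not claim that 1267 was enough. What is missing is the comparison with 1700. This is not a detail left to an unseen analysis plan, since both figures are printed here.
- *Not all 51 need be lost.* Some with missing data may be partly usable. Even at 1267 the shrinkage rule supports only about 11 parameters.

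**Conclusion.** The point holds. The achieved size is 25.5% to 28.5% below the stated requirement, and about 122 to 127 composite cases are expected at 10%, against the stated 200. The 15-predictor capacity is not supported: 10 to 11 parameters if the basis is shrinkage of 0.90, or 12 at 10 events per predictor. For the composite outcome the loss is moderate. It is larger for the outcomes named in the primary objectives and for any window with fewer women, by an amount that the article's figures do not fix.

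This rests on the article's 10% and AUC of 0.75, and for the shrinkage figures on the assumed 0.90 and normal linear predictor. It should be fixed, but it does not undermine the study.

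**What to change.** 1. In Sample Size Estimation, keep 1700 as the planned size and report the achieved size beside it: 1267 enrolled, at most 1216 if all 51 records are excluded, and about 122 composite cases in place of 200. State the period and rate behind the 200, or withdraw it.
2. Replace the limit of "up to 15 predictors" with a cap on candidate parameters, counting polynomial terms. About 10 to 12 suits a composite model. Recompute the cap for each outcome and gestational dataset from its actual women and events before fitting, and state the criterion used. Penalised estimation is an alternative.
3. Name the shortfall among the limitations in the Discussion.

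No further recruitment is needed. The cost is some rewording, a less favourable stated size and a shorter predictor list.
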